## Abstract

**Background:**

Radiofrequency ablation (RFA) is associated with an excellent outcome in the treatment of great saphenous vein (GSV) incompetence. The use of thermal energy as a treatment source requires the instillation of tumescence anesthesia. Mechanochemical endovenous ablation (MOCA) combines mechanical endothelial damage, using a rotating wire, with the infusion of a liquid sclerosant. Tumescence anesthesia is not required. Preliminary experiences with MOCA showed good results and low post-procedural pain.

**Methods/Design:**

The MARADONA (Mechanochemical endovenous Ablation versus RADiOfrequeNcy Ablation) trial is a multicenter randomized controlled trial in which 460 patients will be randomly allocated to MOCA or RFA. All patients with primary GSV incompetence who meet the eligibility criteria will be invited to participate in this trial. The primary endpoints are anatomic and clinical success at a one-year follow-up, and post-procedural pain. The secondary endpoints are technical success, complications, operation time, procedural pain, disease-specific quality of life, time taken to return to daily activities and/or work, and cost-efficiency analyses after RFA or MOCA. Both groups will be evaluated on an intention to treat base.

**Discussion:**

The MARADONA trial is designed to show equal results in anatomic and clinical success after one year, comparing MOCA with RFA. In our hypothesis MOCA has an equal anatomic and clinical success compared with RFA, with less post-procedural pain.

**Trial registration:**

Clinicaltrials NCT01936168

## Background

Varicose veins are a common problem in the Western world. Epidemiological studies show that 21% of adults have some form of varicose veins [1-3], with women being more affected than men [3,4]. The incidence of varicose veins increases steadily with age and is among the top ten complaints for which people visit their general practitioner. The main risk factors include: prolonged standing or sitting, pregnancy, sex and age [5]. The symptoms of varicose veins range from cosmetic complaints to venous ulcers [6].

High ligation and stripping of the great saphenous vein (GSV) has been the gold standard for GSV incompetence for more than 100 years [7]. Surgery is performed under general or spinal anesthesia and is related to a high recurrence rate of 18 to 40% after five years [8,9]. In addition, surgery may lead to significant postoperative symptoms (particularly pain and hematoma) and carries a risk of injury to the saphenous nerve [10,11].

Endovenous techniques have been developed for the treatment of varicose veins [12]. Endovenous laser ablation (EVLA) and radiofrequency ablation (RFA) are now widely accepted techniques and are frequently used in practice [13,14]. They are related to less hematoma, pain, and superior cosmetics and earlier resumption of normal activities and work when compared to traditional surgical stripping [15,16]. Thermal ablative modalities, however, carry the risk of damaging the surrounding tissues of the vein. For this reason, patients are treated with tumescence anesthesia, which requires multiple punctures around the vein. Despite the use of tumescence anesthesia there are still a subset of patients who have postoperative pain, which can last for weeks [17,18].

Mechanochemical endovenous ablation (MOCA), using the ClariVein® device (Vascular Insights, Madison, CT, United States), uses a rotating wire in a catheter to create mechanical damage to the endothelium of the vessel. At the same time, a sclerosant is infused at the end of the catheter, causing chemical damage to the vein wall. With MOCA, the vein wall is not heated and tumescence anesthesia is redundant. Subsequently complications that occur in thermal ablative modalities such as pain, hematoma, induration and nerve injury could be reduced.

The safety and efficacy of MOCA was shown in the first human study [19]. In this study, 30 patients with primary GSV insufficiency were treated using sodium tetradecyl sulfate (Sotradecol). At six months the anatomical success was 97% [19]. After a follow-up period of two years, 27 of the 28 (anatomical success 96%) treated GSV were occluded [20]. Several reports have confirmed the efficacy of MOCA, with occlusion rates varying from 94 to 97% [21-23]. No major complications such as deep vein thrombosis, pulmonary embolism or nerve injury were observed in all previous studies. Moreover, MOCA was associated with lower post-procedural pain and faster recovery than RFA [24]. To date, no studies have been performed to compare MOCA with other endovenous techniques in the treatment of varicose veins. The current study has been designed to compare MOCA for the treatment of GSV insufficiency to RFA in a multicenter randomized controlled trial.

## Methods/Design

### Study design

A prospective multicenter randomized clinical trial was designed to compare RFA and MOCA in the treatment of GSV incompetence. Patients will be included at the outpatient departments of the participating hospitals. The procedures are performed or supervised by dedicated vascular surgeons, who have performed more than 20 procedures of both treatment modalities.

### Study objectives

The aim of the study is to show that MOCA is associated with less post-procedural pain than RFA, with comparable anatomical and clinical success rates.

### Sample size calculation

The assumption has been made that MOCA will have a similar anatomical and clinical success rate at one year when compared to RFA. For a non-inferiority trial with an effect size (anatomical success) of 93% and a margin of 7%, 210 patients per group are needed (alpha 5%, power 80%). The effect size of 93% refers to an estimated anatomical success rate at a one year follow-up period for both groups. Taking into account 10% dropouts in each arm, 230 patients need to be included in each study arm.

A sample size calculation will also be performed for the second primary endpoint on the hypothesis that MOCA will have lower post-procedural pain, as measured by a 100-point VAS (Visual Analog Scale) score during the first two weeks after surgery. To evaluate a 30% reduction in post-procedural pain, 58 patients per group are needed (alpha 5%, power 80%). This analysis will be performed after the inclusion and randomization of at least all 58 patients in each group.

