### Primary endpoints

The primary endpoints are anatomic and clinical success and post-procedural pain after treatment for GSV incompetence with RFA or MOCA. Anatomic success will be measured one year after treatment using duplex ultrasonography. Clinical success will be measured using the Venous Clinical Severity Score (VCSS). Post-procedural pain will be evaluated using a 100-point VAS during the first two weeks after the treatment.

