## Discussion

Since the introduction of minimal invasive modalities for the treatment of great saphenous incompetence, many new techniques have been developed and introduced to the market. While most techniques constantly report anatomical success rates over 90% [13-16], more emphasis is on secondary treatment outcomes such as post-procedural pain, hematoma, quality of life and returning to normal activities. Therefore, the optimal treatment for GSV incompetence is unclear.

The aim of the present randomized trial is two-fold. First, it aims to compare anatomical and clinical success at one year after MOCA, with RFA. Several randomized trials have compared RFA with conventional surgery, endovenous laser ablation and foam sclerosis [12]. These studies showed the superiority of EVLA in terms of anatomical success at one to five years after surgery, although newer radiofrequency devices have similar results [13,28].

Second, it aims to demonstrate that MOCA is associated with a significant reduction in post-procedural pain after treatment. Pain after endothermal ablation is considerable and probably an underreported complication in the literature. Recent studies have shown less post-procedural pain after RFA comparing with EVLA [17,29]. Therefore, accompanied with similar occlusion rates with the newer RFA devices, we have assumed RFA to be one of the 'gold standard’ techniques in minimal invasive treatment for GSV incompetence. In order to have sufficient power, the trial was designed using a non-inferiority principle.

In conclusion, the MARADONA trial is multicenter randomized controlled trial that aims for a reduction in post-procedural pain after MOCA compared with RFA, with a similar anatomical and clinical success.

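### Clinical success is a primary endpoint with a claim of comparability, but the article's only rate, margin and power are for anatomical success, and its analysis section names only difference tests

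*Protocol article*

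**What the plan says.** **Status of the endpoint.** The abstract (Methods/Design) states: "The primary endpoints are anatomic and clinical success at a one-year follow-up, and post-procedural pain". The section Primary endpoints repeats the list without a time point for clinical success: "The primary endpoints are anatomic and clinical success and post-procedural pain after treatment for GSV incompetence with RFA or MOCA". The definitions section makes clinical success a yes/no outcome for each patient, namely a VCSS improvement of at least 1.

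**The claim attached to it.** The abstract's discussion says: "The MARADONA trial is designed to show equal results in anatomic and clinical success after one year". Study objectives asks for less pain with MOCA, "with comparable anatomical and clinical success rates". The main Discussion adds that "the trial was designed using a non-inferiority principle".

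**The sizing.** The section Sample size calculation begins with both outcomes: "The assumption has been made that MOCA will have a similar anatomical and clinical success rate at one year when compared to RFA". The calculation that follows is labelled for one of them: "For a non-inferiority trial with an effect size (anatomical success) of 93% and a margin of 7%, 210 patients per group are needed", at alpha 5% and power 80%. The section then confirms the label: "The effect size of 93% refers to an estimated anatomical success rate at a one year follow-up period for both groups". Pain, called the second primary endpoint, has its own calculation (58 per group for a 30% reduction). No calculation is given for clinical success.

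**The analysis.** Statistical analyses names a t-test or Mann-Whitney test for the follow-up data and Kaplan-Meier curves for obliteration rates, by intention to treat. It mentions no confidence limit to be compared with a margin.

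**The concern.** A claim that two treatments are comparable needs a stated limit on how much worse the new one may be, and a rule that compares a confidence limit with it. For clinical success the article gives neither. Duplex occlusion and VCSS improvement are different outcomes with their own rates, so the 93% does not carry over from one to the other. The VCSS threshold of 1 classifies a patient and is not a between-arm margin.

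If the plan is followed as written, comparability on clinical success would rest on a non-significant difference test, and failing to find a difference does not show that it is small. The alternative is that a margin is chosen after the data are seen. The trial's intended conclusion is less pain with similar anatomical and clinical success, so this affects one of its three parts.

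**Working it through.** **1. Reproduce the article's figure.** Inputs from Sample size calculation: p = 0.93 in both arms, margin 0.07, alpha 5%, power 80%. Formula (unpooled normal approximation): n = (z_alpha + z_power)² × 2p(1−p) / margin².
- One-sided 2.5%: (1.960 + 0.842)² × 2 × 0.93 × 0.07 / 0.07² = 7.849 × 0.1302 / 0.0049 = 208.6, so 209 per group against 210 stated.
- One-sided 5% gives 165.

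The 210 is therefore reproduced for anatomical success with one-sided 2.5%, and that level is used below.

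**2. Power for clinical success.** The documents give no rate or margin for it. Assumptions: equal true rates p in both arms, the 7-point margin borrowed from anatomical success, one-sided 2.5%, 210 evaluable per arm. Formulas: SE = √(2p(1−p)/210); power = Φ(0.07/SE − 1.96).

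| Assumed rate | SE | 0.07/SE − 1.96 | Power | n per arm for 80% power |
|---|---|---|---|---|
| 80% | 0.0390 | −0.17 | 43% | 513 |
| 85% | 0.0348 | 0.05 | 52% | 409 |
| 90% | 0.0293 | 0.43 | 67% | 289 |
| 93% | 0.0249 | 0.85 | 80% | 209 |
| 95% | 0.0213 | 1.33 | 91% | 153 |

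**3. Sensitivity to the margin.** With an assumed 10-point margin, power at 210 per arm is 73% at a rate of 80%, 82% at 85% and 93% at 90%. The smallest margin that keeps 80% power is (1.960 + 0.842) × SE: 10.9 points at 80%, 9.8 at 85%, 8.2 at 90%, 7.0 at 93% and 6.0 at 95%.

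**4. If both success endpoints had to be met.** Assume 93% and 7 points for each. If the two test statistics are independent, joint power is 0.803 × 0.803 = 64%. With a correlation of 0.6 (bivariate normal) it is 70%.

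**5. What a difference test can show.** At an assumed rate of 80%, the 95% confidence interval has a half-width of 1.96 × 0.0390 = 0.077, or 7.7 points. An observed deficit for MOCA of 7 points would then be non-significant, although it equals the margin that the article sets for anatomical success.

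**The case against.** **A journal article condenses the full protocol.** A margin and decision rule for clinical success may stand in a document that is not shown. This stands as a limit on the finding: a reader might infer that no rule exists anywhere, and the article cannot establish that. Simple condensation is not the whole explanation, however, because the article does give sizing for anatomical success and for pain, and its analysis section points to difference tests.

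**Pain is called the second primary endpoint, so the two success outcomes may form the first, with 7 points applying to both.** The reading is possible, because the margin follows a sentence that names both. But no composite is defined, and the calculation is labelled anatomical success. If both had to be met, power would be 64–70% even at 93% each, not 80%.

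**The article never says that clinical success has 80% power.** Correct. A reader might infer it from the opening sentence of the section, but the text ties the 93% to anatomical success twice.

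**The low power figures depend on the chosen inputs.** Also correct. A reader might infer that the trial is clearly underpowered for clinical success. The documents do not support that: nothing in them rules out a rate of 95%, where power is 91%. Just below 93% the loss is modest (75% at 92%), and a wider margin raises power.

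**Conclusion.** The point holds in a limited form. Clinical success is primary in the abstract and in Primary endpoints. The abstract's discussion, Study objectives and Discussion say that it will be shown equal, comparable or similar. The only rate, margin and power for a success outcome are computed for anatomical success, and the analysis section offers only difference tests. The article's design therefore does not support a conclusion of comparable clinical success.

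The size of any power shortfall is unknown. On the assumptions of a 7-point margin, one-sided 2.5%, equal true rates and 210 per arm, power runs from 43% at a rate of 80% to 91% at 95%, and reaches 80% at about 93%. The lack of a stated margin and decision rule matters at every rate. The sizing for anatomical success is sound (209 against 210). This should be fixed, but it does not undermine the trial's sample size for anatomical success.

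**What to change.** Make these changes before any one-year data are viewed by arm:

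- In Sample size calculation, state that the 210 per group and the 80% power refer to anatomical success only, and limit the powered non-inferiority claim to that endpoint.
- In Statistical analyses, report clinical success as the between-arm risk difference with its 95% confidence interval.
- Call clinical success non-inferior only if a margin is prespecified and justified. Say whether the 7 points apply to it and whether both success endpoints must be met, and show its power over a plausible range of rates.
- If the full protocol or the SAP already contains such a margin, cite it and bring the article's wording into line.

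Cost: no extra patients. The power or the claim stated for clinical success becomes less favourable. Recruitment began in July 2013, with 50 patients randomized by December 2013, so the change should be documented as a dated amendment to the protocol or SAP.

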### Setting

Patients will be recruited from the following Dutch centers: Rijnstate Hospital, Arnhem; Antonius Hospital, Nieuwegein; Onze Lieve Vrouwe Gasthuis, Amsterdam; BovenIJ Hospital, Amsterdam; University Medical Center Groningen, Groningen, The Netherlands. In all of the participating centers, each surgeon performing the procedures must have treated at least 20 patients with each technique prior to treating patients who participate in the MARADONA trial to prevent a learning curve bias.

The total study duration will be seven years: the recruitment period will take two years and thereafter patients will be evaluated for a period of five years post-procedure.

### Primary endpoints

The primary endpoints are anatomic and clinical success and post-procedural pain after treatment for GSV incompetence with RFA or MOCA. Anatomic success will be measured one year after treatment using duplex ultrasonography. Clinical success will be measured using the Venous Clinical Severity Score (VCSS). Post-procedural pain will be evaluated using a 100-point VAS during the first two weeks after the treatment.

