### Definitions of terms used for the study

Anatomical success: occlusion of the treated GSV segment, measured with duplex.

Clinical success: objective improvement of clinical outcome after treatment, measured with the Venous Clinical Severity Score (VSCC) of at least 1.

Technical success: initial technical success rate of the procedure, where the catheter can be safely placed at a defined distance from the saphenofemoral junction and the GSV can be treated without technical problems.

Failure of treatment: type 1 (non-occlusion) - the treated vein failed to occlude initially and never occluded during the follow-up; type 2 (recanalization) - the treated vein occluded directly after treatment, but recanalized, partly (>10 cm) or completely, at a later time point during follow-up; type 2a - recanalization of the entire treated segment of the vein; type 2b - partial recanalization (open segment > 10 cm).

Post-procedural complications: complications occurring within 30 days after treatment. Major complications to include deep venous thrombosis, pulmonary embolism, skin burn, saphenous neuralgia. Minor complications to include ecchymosis, superficial phlebitis, hyperpigmentation, induration, wound infection of the puncture site, prolonged pain > one week. Sclerosans-related complications.

Operation time: time of the procedure, starting from puncture of the vein to extracting of the catheter, skin-to-skin contact.

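### Clinical success is a primary endpoint with no assumed rate, margin or power, and no power is given for the joint aim

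*Protocol article*

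**What the plan says.** The section on primary endpoints lists three outcomes: "The primary endpoints are anatomic and clinical success and post-procedural pain after treatment for GSV incompetence with RFA or MOCA". The study objectives combine them in one conclusion: "The aim of the study is to show that MOCA is associated with less post-procedural pain than RFA, with comparable anatomical and clinical success rates". The abstract's discussion and the closing Discussion repeat that combination.

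Clinical success is an outcome of its own, with a yes/no definition: "Clinical success: objective improvement of clinical outcome after treatment, measured with the Venous Clinical Severity Score (VSCC) of at least 1".

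The sample size section treats the three outcomes differently.

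- **Anatomical success:** "For a non-inferiority trial with an effect size (anatomical success) of 93% and a margin of 7%, 210 patients per group are needed", at alpha 5% and 80% power. The article is explicit about the 93%: "The effect size of 93% refers to an estimated anatomical success rate at a one year follow-up period for both groups".
- **Pain:** a separate calculation gives 58 per group for a 30% reduction, at alpha 5% and 80% power. The analysis may be done once at least that many are randomized in each group.
- **Clinical success:** one sentence, shared with anatomical success: "The assumption has been made that MOCA will have a similar anatomical and clinical success rate at one year when compared to RFA".

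On dropout it says: "Taking into account 10% dropouts in each arm, 230 patients need to be included in each study arm".

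The statistical analyses section names Student's t-test or the Mann-Whitney test for the follow-up data, and Kaplan-Meier curves for obliteration. It names no non-inferiority analysis.

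**The concern.** A claim that two treatments are comparable needs a margin fixed in advance. Anatomical success has one and clinical success does not, although both carry the same claim. A t-test or Mann-Whitney test looks for a difference, and failing to find one does not show comparability. As written, the plan has no criterion by which the clinical part of its conclusion could succeed or fail, and a margin could be chosen after the results are known.

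The second issue is power. When several results must all be obtained, the chance of obtaining them together is no greater than the chance of the least likely one. The article gives 80% for anatomical success and 80% for pain, but no figure for the combined aim.

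**Working it through.** **1. Reproduce the plan's figure.** Inputs from the sample size section: p = 0.93 in both arms, margin 0.07, power 80%. The sidedness of alpha is not stated.

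n per arm = 2p(1−p)(z_alpha + z_power)² / margin²

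- One-sided 2.5%: 2 × 0.93 × 0.07 × (1.960 + 0.842)² / 0.07² = 208.6, so 209. This matches the stated 210.
- One-sided 5%: 165, which does not match.

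The anatomical calculation is therefore sound and implies one-sided 2.5%, which is used below.

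**2. Dropout.** 230 × 0.9 = 207, three fewer than 210. Inflating properly, 210/0.9 = 233.3, so 234 per arm.

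Power = Φ(0.07 / √(2p(1−p)/n) − 1.96)

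- n = 210: 80.3%
- n = 207: standard error √(0.1302/207) = 0.0251, and Φ(2.791 − 1.960) = 79.7%

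The shortfall costs about 0.6 percentage points.

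**3. Pain.** No mean or SD is given, so 58 per group cannot be derived independently. Solved backwards (two-sided 5%, 80% power), it implies a standardised difference of (1.960 + 0.842) × √(2/58) = 0.52. With that effect and 207 per arm, power exceeds 99.9%. With 58 per group it is 80%.

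**4. Clinical success and the joint aim.** The documents give no rate or margin. I assume a 7-point margin, equal true rates in the two arms, one-sided 2.5% and 207 per arm, and I vary the rate. The power formula is that of step 2. Under independence, joint power is clinical power × 0.797 × pain power. The last column makes no assumption about dependence. Its lower limit is the sum of the three powers minus 2, and its upper limit is the smallest of the three.

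| Assumed clinical success rate | Power, clinical | Joint, pain on 207 per arm | Joint, pain on 58 per group | Possible range under any dependence (pain on 207) |
|---|---|---|---|---|
| 97% | 98.7% | 79% | 63% | 78–80% |
| 95% | 90% | 72% | 58% | 70–80% |
| 93% | 80% | 64% | 51% | 59–80% |
| 90% | 66% | 53% | 42% | 46–66% |
| 85% | 51% | 41% | 33% | 31–51% |

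Example at 90%: standard error √(0.18/207) = 0.0295; Φ(2.374 − 1.960) = 0.661; 0.661 × 0.797 × 0.9996 = 0.526.

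At any clinical rate the joint power is capped by the anatomical 79.7%.

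**The case against.** **The article is condensed.** The full protocol or analysis plan may hold the success rule and the handling of multiplicity. That stands, and the absence of a formal decision rule is not the point here. But the article does set out the sizing basis for two of its three primary outcomes. For the third it offers only an assumption of similarity, alongside tests that cannot establish comparability.

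**There may really be only two primaries.** The sample size section calls pain the second primary endpoint, and the Discussion calls the aim two-fold. On that reading, success is one endpoint sized on its anatomical part. This is a fair reading, and it is close to the remedy below. But the objectives and definitions keep clinical success separate and include it in the claim.

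**The joint figures rest on assumptions.** This also stands. The clinical rate, its margin and independence are not in the documents. The bar is a one-point VCSS improvement, so rates above 93% are possible, and at 97% almost nothing is lost. Positive correlation between occlusion and clinical improvement would raise joint power above the product. Only the cap of about 80% is free of these inputs.

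**Two stronger readings are not supported.**

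- A reader might infer that the 80% power covers anatomical success alone. It does not, because pain has its own 80% calculation.
- A reader might also infer a family-wise error of 14% from three tests at 5% (1 − 0.95³ = 0.143). That supposes that any single endpoint could carry the claim, whereas the aim is stated as a conjunction. It also conflicts with the one-sided 2.5% that reproduces 210. On that basis, with independent tests, the figure would be 1 − 0.975³ = 7.3%.

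**Conclusion.** The concern holds in a limited form. Clinical success is primary and part of the joint conclusion, but it has no rate, margin or power, and the named tests cannot show that it is comparable. This follows from the text without any assumption.

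Power for the joint aim is not stated and is at most about 80%. How far below depends on the unknown clinical rate: about 79% at 97%, 64% at 93% and 41% at 85% under the assumptions in the working, and lower if pain is tested on only 58 per group. The documents do not establish that joint power is far below 80%. They only leave that open.

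The dropout step is a genuine but very small arithmetic error: 207 evaluable per arm instead of 210, and 79.7% power instead of 80.3%.

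**What to change.** **Preferred.** State that anatomical non-inferiority and pain superiority must both be met, each at its full alpha. No adjustment is needed because both are required. Report clinical success as a key secondary outcome: the difference in proportions with a 95% CI. State the sample on which pain is tested. The pair has joint power of about 80% with pain on the full sample (0.797 × 0.9996), but about 64% with pain on 58 per group (0.797 × 0.80, assuming independence).

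**If clinical success stays primary.** Fix its assumed rate and its margin before any outcome analysis, replace the difference test with a comparison against that margin, and quote the joint power.

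**Minor.** Restate the size as 230 per arm, leaving 207 evaluable and 79.7% power for anatomical success. Alternatively, enrol 234 per arm (468 in total, 8 more).

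**Cost.** The preferred change needs no extra patients. It does alter the status of a primary endpoint after recruitment began (50 randomized by December 2013), so it needs a documented, dated amendment rather than an edit. Inclusion opened in July 2013, so no one-year outcome could exist at that point. Keeping clinical success primary with 80% power of its own could be expensive: with the assumed 7-point margin it needs 289 evaluable per arm at a 90% rate and 409 at 85%.
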